### Shopping Training

The participant will appear in a small version of the grocery store. They will be instructed on how to use the virtual cell phone to check their shopping list, review items in their cart, and answer text messages with the left-hand controller. They will be instructed on how to teleport and select items off the shelf with the right-hand controller. In the shopping training task, the participant must follow specific directions and must correctly put four items in their cart from the shopping list, one of which must be returned to the shelf, and they must answer a text to complete the shopping training. To complete the shopping portion of the task, the participant will need to teleport successfully to multiple shelves and aisles.

### Shopping Experience Number 1

Experience number 1 will be a control experience that will allow the participant to explore the grocery store with no specific task to complete. The shopping environment includes a few avatars and some low music in the background to simulate a realistic shopping environment during off-hours. All shopping actions will be enabled, and the participant may select items and place them in the shopping cart. The only requirement will be that they remain in the environment for 30 minutes. The control experience will evaluate whether the VR environment itself induces significant fatigue that may confound the interpretation of task-specific fatigue induction.

### Shopping Experience Number 2

Experience number 2 is a standard shopping experience designed to mimic a realistic shopping experience during a typical day. Participants will be provided with a shopping scenario. They will be told that they are shopping for sick friends. The participant will try to obtain as many items as possible from the cell phone shopping list. Participants will traverse the grocery store to find objects on the list and place them in the shopping cart. Avatars are present in the store but do not hinder progress or create any specific distractions. The background sound includes typical background noise, music, and overhead announcements. This condition assesses the cognitive load and fatigue related to the mental activity of shopping.

### Shopping Experience Number 3

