### Participants

The participants will be recruited from a local metro region. We anticipate that participant background characteristics (eg, education, ethnicity, sex, and age) will be representative of the metro area in background characteristics (eg, education, ethnicity, sex, and age). Recruitment will be managed by the National Institutes of Health (NIH) Office of Patient Recruitment, using local flyers; Office of Patient Recruitment website; and posts on social media, including Facebook and Twitter. Participants will be remunerated to participate in the study. All protocol activities will take place in a local NIH facility in Bethesda, Maryland. 

For each phase of the study, participants will be healthy individuals aged 18-75 years. Recruitment for phase 1 will target an older (≥55 years) and younger group (18-54 years) with 50% targeted for each group, stratified by sex. Recruiting a broad age range will ensure usability among older individuals, as future apps will likely involve older adult clinical populations. The sample will be stratified by sex, as some research suggests that women may experience immersive VR differently from men [116,117]. The phase 1 sample size will be 24, with 8 participants completing each of the three shopping conditions. Evaluating participants from a variety of backgrounds is important in UX research to identify any systematic issues in the interface, content, or instructions. The phase 2 study recruited 60 healthy individuals aged 18-75 years. For this study, there will be no targeted recruitment of older adults, as any design issues specifically associated with subject age will be addressed before phase 2. The sample size was determined based on the calculated effect sizes of fatigue induction studies that used the VAS-F (Cohen *d*=0.65; SD 0.25) and vigilance decrement studies [34]. The inclusion and exclusion criteria are included in Textbox 1.

Inclusion and exclusion criteria.

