For example, in phase 1, we will compare the participants’ self-reported physical symptoms and eye-related symptoms from the VRSQ before versus after completing the VR shopping experience. We will use the Wilcoxon signed-rank test, given the high probability of a nonnormal distribution in the dependent measure. This comparison will provide evidence to determine whether the VR environment produces physical distress or eyestrain. We computed the total scores for each of the observation scales. These totals inform about the number of times the participant had difficulties with the interface. We will compare the frequencies of interface problems in older and younger and male and female subjects using the chi-square test. These are structured statistical analyses planned as part of the formal UX results. Exploratory procedures are used to identify the relationship between user behavior (eg, number of items reviewed, distance traveled in the environment, and accuracy of shopping behaviors with measures of shopping enjoyment, shopping experience, and sense of immersion in the environment). For these analyses, we used Spearman rank-order correlations.

#### Phase 2

We will use the repeated measures analysis of variance (ANOVA) with the VAS-F and NASA-TLX as repeated dependent variables by shopping experience (fixed) to test the hypothesis that grocery shopping creates fatigue and workload, particularly when the person experiences interruptions and distractions. Secondary analyses will evaluate whether objective indicators of fatigue, such as eye tracking, shopping performance, and cognitive functioning (eg, pre- and postshopping processing speed and working memory) significantly differ by shopping experience using repeated measures ANOVA. A third series of analyses evaluated the relationship among individual characteristics, perceived CF, and workload. We will primarily use correlation to evaluate the relationship among pre-existing symptoms of fatigue, anxiety depression, personality traits, and fatigue susceptibility. Cognitive measures from the NIH toolbox will be correlated with perceived fatigue and workload to identify whether cognitive abilities influence the perception of cognitive workload and fatigue.

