For example, we will use the repeated measures ANOVA to test the primary hypothesis that the cognitive activity of shopping for specific items will create a greater perception of mental workload and fatigue compared with just exploring the environment unless the distribution of dependent measures does not allow for using this specific statistical procedure. Similarly, we will use an appropriate correlation procedure to compare the level of activity measures such as distance traversed in the store, number of items selected and reviewed, and efficiency and accuracy of shopping activity with perceptions of fatigue and workload. Correlation procedures will be used to assess the relationships between constructs, such as personality style, cognitive ability, fatigue susceptibility with self-reported mental workload, and fatigue to identify individual differences in fatigue susceptibility. Eye tracking such as percent eye closure will be explored as a possible objective indicator of fatigue by serving as a dependent measure in the repeated measures ANOVA by shopping experience and in correlational analysis with self-reported fatigue and workload. The actual analysis considers the appropriateness for each specific variable distribution.

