### Strengths and Limitations of This Study

CF is a complex phenomenon influenced by task, environment, personal experience, and individual differences. Our experimental conditions included a familiar task performed in a realistic immersive VR environment that allows for the precise control of stimuli. The ability to control stimuli and timing of events will enable us to determine the relative contribution of distraction, boredom, task complexity, and person characteristics on the development of CF. The strength of the immersive VR experience is the capacity to create a cognitive experience that closely aligns with real-life demands. Our ability to control the presence and timing of interfering factors enables us to assess environmental influences that would be almost impossible to standardize using an actual grocery store.

The immersive VR environment allows us to seamlessly use multiple measures of CF. We will use subjective indicators of CF and workload to better understand how perceived fatigue (eg, physical fatigue: *tiredness* and *sleepiness;* cognitive fatigue: *efficiency* and *difficulty in concentrating*) and workload (eg, mental demand, effort, and frustration) relate to the effects of tasks, environments, and other factors. Potential objective measures of CF, such as changes in behavior (eg, performance efficiency, shopping list rechecking, rate, and the efficiency of movement) and changes in eye movement, can be measured unobtrusively. The use of a randomized controlled design is a strength of this study. Participants will be randomly assigned to 1 of the 3 shopping conditions to control for any confounding effects of person-level background characteristics (eg, age) that may affect fatigue or reactions to the VR experience.

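### The phase 2 correlations of activity, performance and eye-tracking measures with fatigue are described without shopping experience, so arm differences can pass for person-level associations

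*Protocol article*

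**What the plan says.** The phase 2 part of the Analysis section in the protocol article names shopping experience as a fixed factor in the repeated measures ANOVA. The correlations are described separately:

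- Activity and shopping performance: "we will use an appropriate correlation procedure to compare the level of activity measures such as distance traversed in the store", together with items selected and reviewed, efficiency and accuracy, against fatigue and workload.
- Eye tracking: a dependent measure in the ANOVA by shopping experience, and also used "in correlational analysis with self-reported fatigue and workload". Arm is attached to the first use and not to the second.
- Traits, symptoms and cognition: "We will primarily use correlation to evaluate the relationship among pre-existing symptoms of fatigue", with anxiety, depression, personality and fatigue susceptibility. Toolbox cognition scores are correlated with perceived fatigue and workload.

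The only criterion given for choosing a procedure is the distribution of each variable.

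On design, the strengths and limitations section says "Participants will be randomly assigned to 1 of the 3 shopping conditions". Experience 1 lets participants "explore the grocery store with no specific task to complete". Experience 2 is driven by a shopping list. Experience 3 adds obstructed aisles and items and mid-task list changes. The Objectives section hypothesizes more fatigue with structured shopping than with exploration, and more again with interruptions.

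**The concern.** Distance travelled, items handled and efficiency are measured after randomization, and the assigned experience partly determines them. Eye measures may be affected too. The same assignment is expected to move self-reported fatigue and workload. Arm is then a common cause of both variables, and a correlation across all participants mixes two things: how three arm means line up, and whether people who move more or close their eyes more than others in the same condition also feel more tired.

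The first is already covered by the planned ANOVA. The second is what the secondary aims need, because they seek objective indicators of fatigue and individual characteristics that affect susceptibility. At stake is whether a measure is put forward as a fatigue indicator merely because it tracks arm, or is missed because the arm shift runs against it.

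List accuracy has a further problem. Experience 1 sets no task, so it provides no list to be accurate against.

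**Working it through.** **Inputs from the article.** Total size: "The phase 2 study recruited 60 healthy individuals aged 18-75 years". There are three parallel arms. The effect size comes from "fatigue induction studies that used the VAS-F (Cohen *d*=0.65; SD 0.25"). The article does not say whether this d is a pre-post or a between-arm effect.

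**Assumptions.** 20 per arm (60/3, equal allocation); two-sided 5%; within-arm SD of 1 for both variables; all arm shifts, since the article gives none for activity or eye measures. The value 0.65 is borrowed as a plausible fatigue shift.

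**The plan's own figure.** The article states "The sample size was determined based on the calculated effect sizes of fatigue induction studies" but gives no alpha, power or contrast, so 60 cannot be strictly reproduced. At d = 0.65, two-sided 5% and 80% power:

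- Comparison of two arms: 2 × ((1.96 + 0.84)/0.65)² = 37.1, so 38 per arm.
- Within-arm pre-post comparison: ((1.96 + 0.84)/0.65)² = 18.6, so 19.

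Twenty per arm fits only the second reading. This is a further reason not to treat 0.65 as a known step between arms.

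**Formula.** With within-arm correlation ρ, and variances V and covariance C of the three arm means,

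pooled r = (ρ + C) / √((1 + Vx)(1 + Vy)).

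Worked case: fatigue means 0/0.65/0.65 give Vy = 0.0939; measure means 0/1/1 give Vx = 0.2222; C = 0.65 × 0.2222 = 0.1444. With ρ = 0, pooled r = 0.1444/√(1.2222 × 1.0939) = 0.1444/1.156 = 0.125.

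**False positives when ρ = 0.** 20,000 simulated trials per row; pooled Pearson r on 58 df against the arm-adjusted partial correlation on 56 df:

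| Fatigue means (SD) | Measure means (SD) | Pooled r | Pooled rate | Adjusted rate |
|---|---|---|---|---|
| 0/0.325/0.65 | 0/0.325/0.65 | 0.07 | 8% | 5% |
| 0/0.65/0.65 | 0/1/1 | 0.13 | 16% | 5% |
| 0/0.65/0.65 | 0/−1/−1 | −0.13 | 16% | 5% |
| 0/0.65/0.65 | 0/2/2 | 0.20 | 34–35% | 5% |
| 0/0.65/1.3 | 0/0.65/1.3 | 0.22 | 41% | 5% |
| 0/0.65/1.3 | 0/2/2 | 0.28 | 61% | 5% |

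Larger steps in the measure, 1 or 2 SD per arm with fatigue at 0/0.65/1.3, give 67% and 92%. These need control and interference to lie 2 and 4 SD apart on the measure.

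**Masking and reversal.** Take fatigue 0/0.65/0.65 and the measure 1 SD lower in both task arms, so C = −0.1444.

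- ρ = 0.30 appears as (0.30 − 0.1444)/1.156 = 0.13, with power about 17% pooled against 64% adjusted.
- ρ = 0.10 appears as (0.10 − 0.1444)/1.156 = −0.04, the wrong sign.

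**Traits.** These are measured before immersion and balanced in expectation, so Vx = 0 and C = 0, and pooled r = ρ/√(1 + Vy). For ρ = 0.30:

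- Fatigue 0/0.325/0.65: 0.30/√1.0704 = 0.29; power 62.5% against 64.0% adjusted.
- Fatigue 0/0.65/0.65: 0.30/√1.0939 = 0.29; power 61.1% against 63.7%.
- Fatigue 0/0.65/1.3: 0.30/√1.2817 = 0.26; power 53.8% against 63.9%.

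With ρ = 0 the pooled false-positive rate stays at about 5%.

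**The case against.** The omission is read from silence. A partial or within-arm correlation is also a correlation procedure, and the article nowhere says pooled or unadjusted. A condensed article may leave covariates for secondary correlations to a fuller plan. This stands as a limit on the claim: a reader might infer that the sponsor has committed to unadjusted correlations, and the text does not go that far. However, the section presents itself as the statistical analysis plan, ties arm only to the ANOVA, and gives distribution as the only selection criterion. Run as written, the correlations would leave arm out.

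The between-arm part may also be signal. If the conditions induce fatigue and fatigue increases eye closure, a good marker should covary with fatigue across arms, and adjustment removes that part. This stands for eye tracking and is why both results should be shown. It is weaker for activity, where the conditions themselves dictate movement.

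The size is uncertain. The highest rates need very large arm differences, and activity need not rise steadily, because experience 3 obstructs movement while experience 1 allows free roaming. This stands. A reader might infer that the trial will name false fatigue markers; the documents support only that it could.

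Finally, a reader might infer that trait correlations would be spurious too. They would not: randomization leaves only dilution. If fatigue susceptibility means the fatigability scale completed before immersion, its correlations with other pre-immersion measures do not involve arm at all.

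**Conclusion.** The point holds for measures taken during or after shopping. As described, their correlations with fatigue and workload leave out a variable that shapes activity by design and is hypothesized to move fatigue. The consequence ranges from negligible to serious: a false-positive rate of about 8% with small shifts, about 16% to 35% if only control differs, and 41% or more if both variables rise by at least 0.65 SD per arm, against about 5% adjusted. Those figures rest on equal allocation, normal data and assumed shifts.

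For pre-randomization traits the effect is modest attenuation (0.30 to 0.26–0.29) and some loss of power, without false positives.

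The analyses concerned are secondary or exploratory. A reader might take this as a defect in the main result, but the primary ANOVA already contains shopping experience and is untouched. This is a worthwhile improvement to the secondary analyses, not a condition for proceeding.

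**What to change.** In the phase 2 analysis text:

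1. Make the main correlations with fatigue and workload partial (rank) correlations adjusted for shopping experience. With three arms this costs two degrees of freedom (58 to 56 at n = 60).
2. For eye tracking, report the arm-adjusted result beside the pooled one, and say that the pooled result includes differences between conditions.
3. Compute list-based accuracy and efficiency in experiences 2 and 3 only, adjusted for which of the two was assigned. Under equal allocation this leaves 40 of the 60 participants for those measures, a real loss of precision.
4. Treat any arm-by-measure term as optional and exploratory. It adds two degrees of freedom per measure with about 20 people per arm, and it answers a different question from the partial correlation.

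No change to data collection, randomization or the primary analysis is needed.

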The aim of phase 1 is to evaluate the design elements of the virtual shopping environment to identify any factors that may hinder the ability of participants to effectively perform tasks in the virtual environment, identify the risk of physical distress, and obtain user feedback about realism and functionality. The primary hypothesis for the UX study is that the VR environment will be acceptable; however, some users will exhibit minor difficulties using the controllers and interacting with the environment. The primary outcome measures will be observational ratings assessing user difficulties with controller use, interacting with objects, and moving in the environment. The secondary hypotheses include that participants will report only minimal feelings of distress, will report that the virtual grocery store appears realistic and immersive, and will provide a general positive response to the experience with additional helpful ideas about how the experience could be improved.

The primary aim of phase 2 is to evaluate individual and environmental characteristics associated with susceptibility to experiencing CF in the context of performing an IADL, specifically shopping. Our primary hypothesis in phase 2 is that individuals performing structured grocery tasks will report more CF than simple exploratory behavior in the grocery store and that individuals experiencing distractions and interruptions will report more fatigue than those who do not experience interruptions. The primary outcome measure in phase 2 is the self-reported change by participants in CF by shopping experience. The secondary aims of phase 2 are to identify performance and eye-tracking measures that objectively identify fatigue, cognitive abilities, personality characteristics, shopping experience, or transient mood states that affect susceptibility to fatigue during shopping. Specific secondary exploratory hypotheses include that perceived workload increases with time on task for structured tasks and disruptive environments, percent eye closure and gaze shift increase with time on task and are associated with self-reported fatigue, and shopping accuracy declines with time on task.

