Experience number 3 will be the standard shopping experience with frustrating and interrupting events. Participants will be provided the same shopping scenario as experience number 2; however, this shopping experience will be designed to mimic very high traffic, a holiday shopping experience, store crowding, misplaced items, and loud distractions. In addition to environmental stressors, the cell phone will receive *texts* from the friend requesting changes to the grocery list after items have already been selected. Text alerts will be short, repetitive, high-pitched sounds that continue until the text is answered. The progress of the participants will be impeded by an avatar standing in front of a needed item, an aisle blocked for a spill, or a palette blocking access to a specific shelf area. The sounds of a baby crying, people talking, coughing, laughing, and sneezing are present. The music and announcements are played at a slightly higher volume than in the standard shopping condition. This condition will assess the cognitive load and fatigue related to the mental activity of shopping in the presence of distractions and frustrating events.

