### Fatigue Assessment

Fatigue induction studies evaluate real-time changes in fatigue symptoms by self-reporting, performance, and eye tracking. An adapted version of the Visual Analog Scale–Fatigue (VAS-F) [97] will be used as a state fatigue measure given its history of use in fatigue induction research. [27,98,99] A closely linked concept to CF is cognitive workload. Cognitive workload applies an ergonomic and human factors model (eg, elements of a job or task that create a feeling of mental work) to understand fatigue as it relates to sustained work performance [100-104]. The NASA-TLX is a commonly used measure of workload [105,106]. In addition to subjective measures, there are two approaches to use performance data to objectively measure fatigue: change in performance on the induction task or using a pre- versus postintervention cognitive assessment [26,29,107,108]. Tests of reaction time [42], working memory [23], and inhibitory control [32] are used to assess fatigue effects.

Psychophysiological measures identify objective brain or autonomic nervous system indicators of fatigue using EEG (electroencephalogram) [22,23,30,109], ERP (event related potential) [28,31,86,110], functional brain imaging [27,40,107,108], and ECG (electrocardiogram) [29,30] to measure changes in brain or cardiovascular activity associated with fatigue. Of the various physiological indicators, eye tracking has emerged as a promising, noninvasive tool for identifying objective measures of CF. Eye tracking studies show changes in blink rate, percent eye closure, gaze fixation (eg, length and location), and gaze shift rate are associated with CF [30,49-51,111-114]. Changes in gaze shift rate may indicate use of less efficient lower-level cognitive processing [49] and a centralized fixation can indicate a loss of full attention to the task [115]. Several sources, using different task demands, show changes in visual activity as the time on task increases.

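### Part of the planned correlation between logged shopping efficiency and perceived fatigue could reflect awareness of performance, because efficiency is also an example of perceived cognitive fatigue

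*Protocol article*

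**What the plan says.** Only the protocol article is at hand. These statements bear on the point:

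- **The planned analysis** (Methods, Analysis, Phase 2). Distance travelled and other activity measures are to be correlated with self-report, including "number of items selected and reviewed, and efficiency and accuracy of shopping activity with perceptions of fatigue and workload".
- **The content of the self-report** (Discussion, Strengths and Limitations). Perceived fatigue is described by example. Physical fatigue is illustrated by tiredness and sleepiness, and the cognitive part by "cognitive fatigue: *efficiency* and *difficulty in concentrating".
- **The candidate marker** (same paragraph). "Potential objective measures of CF, such as changes in behavior (eg, performance efficiency, shopping list rechecking, rate, and the efficiency of movement" are among the measures to be recorded unobtrusively.
- **The aim served** (Objectives). A secondary aim of phase 2 is to "identify performance and eye-tracking measures that objectively identify fatigue". The Phase 2 analysis text likewise lists "objective indicators of fatigue, such as eye tracking, shopping performance, and cognitive functioning".
- **The instrument** (Fatigue Assessment). "An adapted version of the Visual Analog Scale–Fatigue (VAS-F) [97] will be used as a state fatigue measure". The number, wording and scoring of the items are not given.

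Nothing in the article separates the efficiency content of the rating from the rest when the rating is set against logged efficiency.

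**The concern.** Efficiency stands on both sides of the planned correlation: recorded by the software on one side, and named as part of the self-report on the other. Someone who found few items and knows it may rate their efficiency low without being tired. That would produce a correlation in the expected direction with no fatigue involved.

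Shopping Experience Number 3 supplies an obvious reason for such awareness: "The progress of the participants will be impeded by an avatar standing in front of a needed item", and aisles and shelf areas are blocked as well. Participants in that arm can know that they shopped slowly for reasons unrelated to fatigue. The overlap operates between individuals through shared item content, so comparing or adjusting by shopping experience does not remove it.

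At stake is the secondary aim of finding performance measures that identify fatigue objectively. A correlation built partly on awareness of performance would be weak support for calling efficiency such a measure.

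**Working it through.** The article states no figure for this correlation, so there is none to reproduce. The calculation below shows how large the artefact could be under stated assumptions.

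**Inputs from the article**
- Phase 2 sample size: 60, in three arms (Participants; Study Design).
- The exploration arm has no specific task (Shopping Experience Number 1), so list-based efficiency is meaningful in two arms only. If the arms are equal (an assumption), that is 60 / 3 × 2 = 40 people.

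**Assumed inputs**
- The fatigue score is the sum of K equally weighted items, all oriented the same way, with a common inter-item correlation ρ.
- One item, efficiency, correlates r with logged efficiency. Every other item is unrelated to it, and logged efficiency has no link with fatigue.
- Base case r = 0.5 and ρ = 0.5; range r = 0.3 to 0.7 and ρ = 0.3 to 0.5.
- K is not stated, so 2, 4, 10 and 18 are shown.
- Each test is two-sided at 5%.

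**Formulas**
- Artefactual correlation: c = r / √(K + K(K − 1)ρ).
- Chance of a significant result, by Fisher's z: with m = atanh(c) × √(n − 3), it is Φ(m − 1.96) + Φ(−m − 1.96).

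**Base case, n = 40**
- K = 2: c = 0.5 / √(2 + 2 × 1 × 0.5) = 0.5 / √3 = 0.29. Here m = 0.297 × 6.08 = 1.81, so the chance is Φ(−0.15), about 44%.
- K = 4: c = 0.5 / √(4 + 4 × 3 × 0.5) = 0.5 / √10 = 0.16; about 16%.
- K = 10: c = 0.5 / √(10 + 10 × 9 × 0.5) = 0.5 / √55 = 0.07; about 7%.
- K = 18: c = 0.5 / √(18 + 18 × 17 × 0.5) = 0.5 / √171 = 0.04; about 6%.

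**Over the assumed range, n = 40**

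| Items in score | Artefactual correlation | Chance of p < 0.05 |
|---|---|---|
| 2 | 0.17 to 0.43 | 19% to 81% |
| 4 | 0.10 to 0.25 | 9% to 35% |
| 10 | 0.04 to 0.12 | 6% to 11% |
| 18 | 0.02 to 0.07 | 5% to 7% |

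**With the efficiency item left out.** Under the same model the remaining items are unrelated to logged efficiency, so c = 0 and the rejection rate returns to 5%. That depends on the assumption that awareness of performance reaches no other item.

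**The case against.** The strongest reply is that the article does not show the overlap to be large, or even that the item is a verdict on the shopping. Efficiency appears only as an example in a Discussion parenthesis. The scale is described as a state measure and is also given at baseline (Study Design), before there is any shopping to judge. An item repeated at every time point may well ask how efficient the person feels. The size also depends heavily on the length of the score, and a long total score would make the artefact negligible. These points stand. They limit the concern to something that could happen, of unknown size.

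It is also fair to say that this correlation is not the only evidence on shopping performance, which is also compared across shopping experiences by repeated measures ANOVA. No rule in the article says that a significant correlation validates a marker, and the specific secondary hypotheses are labelled exploratory. Eye tracking and the pre- and post-shopping cognitive tests do not share this item content. This lowers the stakes but leaves the overlap in place, and experience 3 reduces efficiency by design, so the comparison between experiences does not settle the matter either.

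Finally, dropping one item need not give a clean score. Someone aware of having shopped badly may also report difficulty in concentrating. This stands too, and is why the re-scored result should be shown beside the full score and read with caution, not used as a pass-or-fail test of validity.

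What the reply does not remove is the combination stated in the article: efficiency is an example of the perceived state, efficiency is a candidate objective marker, and the two are to be correlated. That is not detail left to a fuller document.

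**Conclusion.** The concern holds in a limited form. Part of any correlation between logged shopping efficiency and perceived fatigue could reflect awareness of performance, and the article describes no safeguard. Under the base assumptions the artefact matters for a short cognitive-fatigue score (0.29 for two items, 0.16 for four) and is close to nothing for a long one (0.07 at 10 items, 0.04 at 18). A short score is plausible, because the outcome of interest is cognitive fatigue and the article distinguishes cognitive from physical content, but it is not stated. The values of r and ρ have no source in the article.

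A reader might infer that the overlap by itself makes efficiency look valid, or that the two sides measure the same thing. The article does not support that: the item wording is unknown, and logged behaviour and a felt state are not identical. A reader might also apply the calculation to all 60 participants, which gives higher rejection rates. For list-based efficiency that is not justified, since one arm has no list. Nor does the point touch the primary VAS-F comparison between shopping experiences.

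**What to change.** For the secondary correlations of shopping efficiency and accuracy with perceived fatigue, add to the analysis plan:

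1. Report each correlation twice, side by side: with the full fatigue score, and with the score computed without its efficiency item(s).
2. If the association appears only when the efficiency item(s) are included, do not interpret efficiency as an objective indicator of fatigue.
3. State that awareness of performance may still affect other items, such as difficulty in concentrating, so an association that survives re-scoring is supportive and not conclusive.

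Leave the primary VAS-F analysis unchanged.

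The cost is one alternative scoring of data already being collected and a few sentences of text. The downside is a slightly shorter and less reliable score in these exploratory correlations.
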